### ***Control/Standard-care***

Local medical, psychiatric and family medicine services provide routine care according to their clinical judgment and available resources. Standard-care will be ascertained by the participant's treating physician based on the patient's clinical needs. Research staff will record the nature and intensity of standard-care delivered to each participant. In current practice, MDD patients are not routinely referred for any psychological therapies in Pakistan. Standard-care in Pakistan largely comprises of pharmacotherapy.

## **Outcome measures**

A form will be designed to collect sociodemographic and clinical characteristics from the medical records, and this information will be confirmed in a clinical interview. HDRS scores will be used to inform two primary outcomes measures: estimated time from randomization to response ( $\geq 50\%$  reduction from baseline) and remission (HDRS score  $\leq 7$ ) (Hamilton, 1960).

Secondary outcome measures will include: severity of depressive symptoms (HDRS score), severity of manic or hypomanic symptoms according to the (YMRS score) (Young et al., 1978). An additional checklist with six common side effects (dry mouth, diarrhea or constipation, dizziness or drowsiness, loss of appetite or nausea, headache, and excessive sweating), along with FISBER, will be used to measure side effects at each treatment visit. The pill count method will be used to measure treatment adherence.

## **Assessment Procedure**

This trial will include two experienced treatment-blind assessors at each site, who will independently administer the mentioned outcome measures at baseline and at 2, 4, 8, 12, and 24 weeks. The research coordinator at each site will advise and remind patients at each visit about non-disclosure of their treatment groups to the assessor.

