Major treatment guidelines from high-income countries emphasize the importance of 'Measurement-Based Care' (MBC), which utilizes outcomes based on validated clinical instruments to

guide treatment decisions (Aboraya et al., 2018; Gelenberg, 2010; Kennedy et al., 2016). This concept was derived from the stepwise treatment algorithm developed through the Sequenced Treatment Alternatives to Relieve Depression (STAR\*D) trial (Trivedi, 2009; Trivedi, Rush, et al., 2006; Trivedi & Daly, 2007). The large-scale trial funded by the US National Institute of Mental Health examined treatment options in an algorithmic manner with the aim to guide the next steps for treatment of patients with MDD who have an inadequate response to an antidepressant. The trial reported significantly improved outcomes, better-informed treatment decisions and greater remission rates in patients with chronic depression. Similarly, in a study of 120 patients with moderate to severe MDD in China, significantly more patients receiving MBC achieved response (86.9% compared with 62.7%) and remission (73.8% compared with 28.8%) compared to those receiving standard care (Guo et al., 2015). Time to response and remission were significantly shorter with MBC (for response, 5.6 weeks compared with 11.6 weeks, and for remission, 10.2 weeks compared with 19.2 weeks). There was also a significantly larger decrease in Hamilton Depression Rating Scale (HDRS) scores (-17.8 compared to -13.6) in the MBC group. The MBC group had significantly more treatment adjustments (44 compared with 23) and higher antidepressant dosages from week 2 to week 24 (Guo et al., 2015). MBC has also been found to help patients gain insight into their illness course; those who completed self-reports of depressive symptoms expressed that the measures allowed them to quantify their symptoms and gain a better understanding of their experience with depression (Dowrick et al., 2009). The better educated patients are about these measurements, the more they adhere to a treatment plan (Trivedi et al., 2020). MBC may also be a valuable tool for facilitating collaborative care among providers within and across organizations (Katon et al., 2010). Given MBC's potential to improve outcomes, it may be one of the minimal interventions necessary for maximal improvement in clinical outcomes in patients with MDD (R. Kessler & Glasgow, 2011).

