### **Sample size**

The sample size of 120 participants for this exploratory trial is based on the study conducted by Guo et al. 2015(Guo et al., 2015).

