### **2. Outcomes**

A form will be designed to collect sociodemographic and clinical characteristics from the medical records, and this information will be confirmed in a clinical interview. HDRS scores will be used to inform two primary outcomes measures: estimated time from randomization to response (defining response as  $\geq 50\%$  reduction in HDRS from baseline) and remission (defined as HDRS score  $\leq 7$ ) (Hamilton, 1960).

Secondary outcome measures will include changes in severity of depressive symptoms (HDRS score). An additional checklist with six common side effects (dry mouth, diarrhea or constipation, dizziness or drowsiness, loss of appetite or nausea, headache, and excessive sweating); and the FISBER, will be used to measure side effects at each treatment visit. The pill count method will be used to measure treatment adherence.

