### 3.2. Statistical Analyses

A treatment-blind statistician will analyze the data after completion of follow-ups for all recruited participants using SPSS for Windows, version 20.0 (IBMCorp., Armonk, N.Y.).

Like the Guo et al. (2015) trial, we will use independent-sample t-tests, Mann-Whitney U tests, and chi-square tests, to compare sociodemographic and clinical characteristics, discontinuation, response and remission rates, and side effects as appropriate. Full intent-to-treat analyses will be carried out to determine all-cause discontinuation. Estimated time from randomization to response and remission will be calculated using Kaplan-Meier survival analyses, and a comparative analysis will be facilitated using the Cox proportional hazards regression model. Analysis of covariance will be used to compare the changes in HDRS scores between the two groups. Additional subgroup analysis might be carried out to understand group-differences due to age, gender, duration of illness, and number of previous episodes. The significance threshold will be  $p < 0.05$  (two-tailed) for all analyses.

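### Primary event times are seen only at five HDRS visits, but the SAP plans plain Kaplan-Meier and Cox: reported weeks will run late and their difference too small, and the hazard ratio depends on an unstated tie method

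*Combined protocol and SAP*

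**What the plan says.** SAP section 2 sets the primary endpoints: "HDRS scores will be used to inform two primary outcomes measures: estimated time from randomization to response" (at least a 50% fall in HDRS from baseline) and to remission (HDRS 7 or below). The protocol's Assessment Procedure has blinded assessors who "will independently administer the mentioned outcome measures at baseline and at 2, 4, 8, 12, and 24 weeks". Table 1 of the protocol has further decision points at weeks 6 and 10, but they use the self-rated QIDS-SR and so do not narrow the HDRS intervals.

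On estimation, SAP 3.2 states: "Estimated time from randomization to response and remission will be calculated using Kaplan-Meier survival analyses". To contrast the arms, the same section says that "a comparative analysis will be facilitated using the Cox proportional hazards regression model". The work is to be done "using SPSS for Windows, version 20.0". Neither the protocol's Statistical analysis section nor SAP 3.2 mentions interval censoring, grouped time, a tie method, or how an event between visits is dated. No power or event target is given: "The sample size of 120 participants for this exploratory trial is based on the study conducted by" the replicated trial.

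**The concern.** The gaps between HDRS ratings are 2, 2, 4, 4 and 12 weeks. A patient who remits in week 13 and one who remits in week 23 both first show it at week 24. Unqualified Kaplan-Meier and Cox would naturally take the visit date as the event date, and all events would then fall on five tied times.

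Two things are at stake:

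- **The weeks themselves.** They are the primary quantity and would partly reflect the visit calendar. The arm with faster events can be shifted more, which distorts the contrast.
- **The Cox comparison.** With only five distinct event times, the choice of tie approximation can change the hazard ratio and the power, and the SAP leaves that choice open.

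**Working it through.** **Inputs.** HDRS visits at weeks 2, 4, 8, 12 and 24; 120 patients randomised 1:1, so 60 per arm; two-sided 0.05. From the protocol's account of the replicated trial (MBC v standard care): response 86.9% v 62.7%, remission 73.8% v 28.8%; times 5.6 v 11.6 weeks (response) and 10.2 v 19.2 weeks (remission). The plan has no power calculation to reproduce. Assumptions throughout: visits on schedule, an event persists to the next visit, dropout is non-informative (0% or 20%).

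**1. Shift in the reported weeks, constant hazards.**
λ = −ln(1 − p24)/24. True mean restricted to 24 weeks = p24/λ. Recorded mean = Σ (interval length × S at interval start).

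Remission, MBC: λ = 0.0558; true 0.738/0.0558 = 13.2. Recorded 2×1 + 2×0.894 + 4×0.800 + 4×0.640 + 12×0.512 = 15.7.
Remission, standard care: λ = 0.01415; true 20.3. Recorded 2×1 + 2×0.972 + 4×0.945 + 4×0.893 + 12×0.844 = 21.4.

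| | True MBC / standard | Recorded MBC / standard | Difference, true → recorded |
|---|---|---|---|
| Response | 10.26 / 15.26 | 12.91 / 17.44 | 5.00 → 4.53 (−9%) |
| Remission | 13.22 / 20.35 | 15.69 / 21.42 | 7.12 → 5.73 (−20%) |

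The times run 1.1 to 2.7 weeks late, more so under MBC.

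**2. The same, matched to the reported times as well as the rates.** Constant hazards do not reproduce the replicated trial's times. Take S(t) = exp[−H(t/24)^k] with H = −ln(1 − p24), and choose k so that the restricted mean equals the reported time (assuming that is what the reported time is). This gives k of about 0.32 in both arms for response, and 0.48 and 0.50 for remission.

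| | True MBC / standard | Recorded MBC / standard | Difference, true → recorded |
|---|---|---|---|
| Response | 5.6 / 11.6 | 7.40 / 13.04 | 6.0 → 5.65 (−6%) |
| Remission | 10.2 / 19.2 | 11.99 / 20.02 | 9.0 → 8.03 (−11%) |

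The times run 0.8 to 1.8 weeks late. A rising hazard (k = 1.5) gives delays of up to 3.4 weeks and larger shrinkage (response 4.26 → 3.49, remission 5.93 → 4.14), but its true times lie further still from those reported.

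**3. Hazard ratio.** The true ratio is ln(1 − 0.869)/ln(1 − 0.627) = 2.06 for response and ln(1 − 0.738)/ln(1 − 0.288) = 3.94 for remission. With risk-set shares r and event shares d at each visit (1 = MBC, 0 = standard care), the large-sample Breslow estimate solves
Σ [d1 − (d1 + d0)·r1·e^β/(r1·e^β + r0)] = 0.
Under constant hazards this gives 1.83 (−11%) for response and 3.44 (−13%) for remission. For response, the curves in step 2 give 1.76. The Efron limit for response under constant hazards is 2.04.

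**4. Response power.** 3,000 simulated trials per row, 60 per arm, each event moved to the next visit:

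| Scenario | Exact times (unattainable) | Breslow | Efron | Grouped-time |
|---|---|---|---|---|
| Constant hazards | 92.8% | 84.7% | 91.7% | 92.4% |
| With 20% dropout | 89.9% | 81.2% | 88.1% | 88.6% |
| k = 1.5 | 92.6% | 80.1% | 91.3% | 92.2% |
| Smaller effect (assumed 75% v 62.7%) | 32.9% | 22.0% | 32.1% | 33.3% |
| No effect (type I error) | 4.9% | 2.5% | 4.8% | 5.0% |

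Breslow loses 8 to 13 points against exact times and about 7 to 11 against Efron. At k = 1.5 its mean response hazard ratio is 1.75 (−15%). Remission power at the replicated rates is at least 99.5% under every method. At a smaller assumed remission effect (48% v 28.8%) it is 58.4% exact, 52.9% Breslow and 58.3% Efron. Under constant hazards without dropout the grouped-time model gives mean hazard ratios of 2.09 (response) and 4.02 (remission).

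**The case against.** A reader might infer that the visit schedule by itself shrinks the hazard ratio and costs power. The documents do not support that. The loss needs Breslow ties, and the plan names the package but not the tie method. What that package does by default is not in the documents. With Efron ties the loss nearly disappears.

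A reader might also note that the replicated trial's standard-care remission time of 19.2 weeks ("for remission, 10.2 weeks compared with 19.2 weeks") lies in the week 12 to 24 gap, and conclude that control remissions mostly occur there. That does not follow. Only 28.8% remitted, so 19.2 cannot be a Kaplan-Meier median. Read as a mean restricted to 24 weeks without dropout, non-remitters contribute 24 × 0.712 = 17.1 weeks, leaving (19.2 − 17.1)/0.288, or about 7.3 weeks, as the mean among remitters. Constant hazards would put 38% (response) and 46% (remission) of standard-care events in that gap; curves matched to the reported times put 13% and 26% there.

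Further points stand. No method tested inflates type I error, so a positive result would not be spurious on this account. The chi-square comparisons of rates and the ANCOVA on HDRS do not depend on dating events between visits. The trial calls itself exploratory and states no power, so none is contradicted. As a direct replication, it has reason to keep the same analysis available.

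The late and unequal shift in the reported weeks survives all of this, because it needs no assumption about ties.

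**Conclusion.** The concern holds in two parts of different strength.

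- **Weeks.** If events are dated at visits, which is the natural reading of SAP 3.2 though not stated there, restricted mean times are late by roughly 1 to 3 weeks. The between-arm difference is understated by about 11% to 20% for remission and 6% to 9% for response. The lower figures come from curves fitted to the replicated trial's rates and times, the higher from constant hazards.
- **Hazard ratio and power.** These are affected materially only under Breslow ties: the response hazard ratio is 11% to 15% low, response power about 7 to 13 points low, and type I error near 2.5%. Under Efron ties or a grouped-time model the hazard ratio is within about 3% and power within about 2 points of exact times. Which case applies cannot be settled from the documents.

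The direction is conservative, and remission power is barely affected at the replicated trial's effect. The matter should be settled before analysis because both primary outcomes are times and a better method exists for data already being collected.

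**What to change.** In SAP 3.2:

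1. State that response and remission are interval-censored between HDRS visits.
2. Make the primary comparison a grouped-time proportional-hazards model: binomial regression with a complementary log-log link, one record per patient per HDRS visit until the event or the last visit attended, with visit indicators, arm and any prespecified covariates. The exponentiated arm coefficient is still the hazard ratio. At minimum, keep Cox and name Efron or exact ties, after confirming that the named software offers the choice.
3. Report cumulative response and remission at each visit, or interval-censored estimates of time, in place of mean weeks based on visit dates.
4. Keep visit-date Kaplan-Meier and Cox as a labelled secondary analysis for comparison with the replicated trial.

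The cost is SAP wording and a reshaped dataset; no new data are needed. The small downside is that headline weeks will be comparable with the replicated trial only through the secondary analysis.

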## Statistical analysis

We will analyze the data using SPSS for Windows, version 20.0 (IBM Corp., Armonk, N.Y.). Similar to the Guo et al. (2015) trial, we will use independent-sample t-tests, Mann-Whitney U tests, and chi-square tests, to compare sociodemographic and clinical characteristics, discontinuation, response and remission rates, and side effects as appropriate. Full intent-to-treat analyses will be carried out to determine all-cause and specific-cause discontinuation. Estimated time from randomization to response and remission will be calculated using Kaplan-Meier survival analyses, and a comparative analysis will be facilitated using the Cox proportional hazards regression model. Analysis of covariance will be used to compare the changes in HDRS and YMRS scores between the two groups. Additional sub-group analysis might be carried out to understand group-differences due to age, gender, duration of illness, and number of previous episodes. The significance threshold will be  $p < 0.05$  (two-tailed) for all analyses. A treatment-blind statistician will carry out interim quality checks and efficacy analysis, while final evaluation will be carried out after completion of followups for all recruited participants.

## Ethical and safety considerations

The trial will be conducted and reported as per recommendation of the CONSORT statement for RCTs. National Bioethics Committee (NBC) of Pakistan has given full ethics approval. All members of the research team will comply with the International Conference on Harmonization Good Clinical Practice (ICH-GCP) guidelines. Research staff will be trained on Good Clinical Practices (GCP) and will not begin data collection until the GCP certification is successfully completed. All the information provided by the participants will be kept confidential and authorization will be required prior to access. Patient identifying information will not be published. Participation to the trial will be voluntary and participants will have the right to withdraw from the study at any time, without giving any reason. Withdrawal from the trial will have no effect in routine care. Informed consent forms will be in the local language for those participants who can read. Participants, who are unable to read and write, will be provided with verbal information (in the local language) that will encompass all aspects of the participant written informed consent form. The participants will then sign the consent form and a caregiver will sign alongside. However, if they cannot write, the participant's caregiver will sign alongside the participant's thumbprint. The PIS and the participant informed consent form will include details of the purpose of the study; the opportunity to ask questions; voluntary participation in the study and the right to withdraw from the study at any time, for any reason; and privacy and confidentiality. All participants can decide to participate right

away if they want to, or they will be given at least 48 hours to read and discuss queries with family or the research team before a decision for participation is made.

We do not anticipate any major risks related to the intervention. However, we acknowledge that potentially vulnerable people with mental illness will be participating in the trial. Some topics discussed or questions asked in the sessions/assessments may cause distress, and in such instances, appropriate support will be provided. We will map available mental health resources ensuring pathways to care. The research team has considerable clinical and research experience, including the management of difficult situations arising in research interventions and interviews. In case participant recruited to this study experience active suicidal ideation or subsequently identified as needing more intensive treatment will be appropriately referred for psychiatric evaluation and treatment. Patients will be removed from the study if they report suicidal attempt, became pregnant, developed a severe medical condition, or suffered from newly emerging side effects that they find intolerable and that could not be managed. Patients who will be removed from the study will receive antidepressant treatment as appropriate as part of clinical care. Research staff will be provided with regular supervision throughout the duration of the project. We already have study protocols in place that include details about how to manage difficult situations arising in research, safety and lone working arrangements. In the event of any study-related injury or adverse event, intervention and treatment will be available from medical staff. Any adverse events will be reported to the REB within the required timeframe.

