### **Study Intervention and Procedure**

After providing informed consent, eligible patients will enter a one-week washout phase to eliminate any effects of psychotropic medications previously taken. After washout week, the patients will be assigned to treatment arms based on randomization schedule, where they will receive either **open-label paroxetine**

(10–50mg/day) or open-label mirtazapine (7.5–45mg/day). All patients will be followed for 24-weeks after randomization. This dosage range is recommended by the US Food and Drug Authority (*Paxil - Highlights of Prescribing Medication*, 2022; *Remeron -Highlights of Prescribing Medication*, 2022). Paroxetine is a commonly prescribed antidepressant, working as a selective serotonin reuptake inhibitor, while Mirtazapine, which works as an alpha-2 antagonist, has a different mechanism of action. Similar to the Guo et. al study (Guo et al., 2015), the decision about the prescription of drug and dosage will be made by the treating psychiatrists/GP. Depending on the duration of prescribed dosage, symptoms and side effects, the psychiatrist/GP will make adjustments. In case of intolerability or inefficacy, one medication change between paroxetine and mirtazapine will be allowed. Short-acting benzodiazepines, prescribed occasionally for agitation, anxiety, and insomnia, will be permitted, as well as any other medications not affecting the CNS.

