## **Contents**

### **1. Specific Aims and Hypotheses**

### **2. Outcomes**

### **3. Statistical Methods**

#### **3.1. Interim Analyses**

#### **3.2. Statistical Analyses**

### **1. Specific Aims and Hypotheses**

The aim of this trial is to determine the efficacy and safety of MBC in patients with MDD in comparison with standard care in Pakistan. To reduce the variance found in treatment-as-usual and isolate the impact of MBC, this trial will limit medication choices to either paroxetine or mirtazapine (as per previously published trials). We hypothesize that, compared to standard care group, the MBC group will have significantly higher rates and shorter times to response and remission, along with lower rates of dropout and side effect burden.

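### Removal from the study ends HDRS follow-up for reasons plausibly linked to outcome, and the plan does not say how removed patients enter the two primary analyses

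*Combined protocol and SAP*

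**What the plan says.** **Follow-up.** The protocol (Study Intervention and Procedure) states: "All patients will be followed for 24-weeks after randomization". Under Assessment Procedure, blinded HDRS ratings fall at baseline and weeks 2, 4, 8, 12 and 24.

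**Removal.** The protocol (Ethical and safety considerations) states: "Patients will be removed from the study if they report suicidal attempt, became pregnant, developed a severe medical condition". The remaining ground for removal is side effects that are new, intolerable to the patient and beyond management. Removed patients then receive antidepressant treatment as part of clinical care. No later HDRS rating is mentioned for them.

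**Primary outcomes and analysis.** SAP section 2 states: "HDRS scores will be used to inform two primary outcomes measures: estimated time from randomization to response", and the second is time to remission. SAP section 3.2 states: "Estimated time from randomization to response and remission will be calculated using Kaplan-Meier survival analyses", with a Cox model for the comparison. Response and remission rates are also compared, by chi-square.

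**Analysis population.** Intent-to-treat appears once in each document, tied to discontinuation. The protocol (Statistical analysis) has "Full intent-to-treat analyses will be carried out to determine all-cause and specific-cause discontinuation"; SAP section 3.2 has "Full intent-to-treat analyses will be carried out to determine all-cause discontinuation". Neither document gives an analysis population for response or remission, a censoring or competing-event rule, a missing-data method, a denominator for the rates, or a sensitivity analysis for removed patients.

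**The concern.** A patient removed before responding has no further HDRS. If nothing else is specified, Kaplan-Meier and Cox software will censor that patient at the last assessment. The analysis then assumes that removed patients would have gone on to respond or remit at the same rate as those who stayed. For a suicide attempt or unmanageable side effects that assumption is doubtful.

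It matters more here because the trial expects the arms to differ in attrition. SAP section 1 hypothesises that MBC will do better on response and remission, "along with lower rates of dropout and side effect burden". MBC is also a strategy whose schedule acts on side effects, so tolerability failures are part of what is being compared.

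Two defensible analyses of the same data could then give visibly different primary results, and nothing in the SAP chooses between them before the data are seen.

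**Working it through.** The plan has no figure of its own on this point: it states no dropout or removal rate. The check first compares the passages, then sizes the consequence under stated assumptions.

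**1. The passages side by side.** Follow-up to week 24 for all patients and removal from the study cannot both hold for a patient removed at, say, week 6, unless removal means only stopping study treatment. The text does not say that. Only patients removed before their event are affected; an event already observed counts.

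**2. Inputs.**
- From the protocol's Introduction, the rates in the replicated trial: response 86.9% (MBC) and 62.7% (standard care); remission 73.8% and 28.8%.
- From Assessment Procedure: visits at weeks 2, 4, 8, 12 and 24.
- Assumed: constant hazards; a proportion r removed, uniformly over weeks 0–12; removal independent of the underlying response time; no response observed after removal; r between 5% and 20%.

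**3. Share of randomised patients with an observed response.** With λ = −ln(1 − p)/24 and F(t) = 1 − exp(−λt), a patient removed in weeks 2–4, 4–8 or 8–12 can have a response recorded only by the visit at week 2, 4 or 8. So

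q = (2/12)F(2) + (4/12)F(4) + (4/12)F(8), and share = (1 − r)p + rq.

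- MBC: λ = 0.0847 per week; F(2), F(4), F(8) = 0.156, 0.287, 0.492; q = 0.286.
- Standard care: λ = 0.0411; F(2), F(4), F(8) = 0.079, 0.152, 0.280; q = 0.157.

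Example, 5% removed in MBC and 20% in standard care: MBC 0.95 × 0.869 + 0.05 × 0.286 = 0.840; standard care 0.80 × 0.627 + 0.20 × 0.157 = 0.533; difference 0.307.

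| Removed, MBC / standard | Kaplan-Meier difference, censored at removal | Difference in share with observed response |
|---|---|---|
| 5% / 20% | about 24 points | 84.0 − 53.3 = 31 |
| 10% / 10% | about 24 points | 81.1 − 58.0 = 23 |
| 20% / 5% | about 24 points | 75.2 − 60.4 = 15 |

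The Kaplan-Meier column stays at 86.9 − 62.7 = 24.2 because removal is independent of response by construction. Simulation with the same assumptions gave the same results. For remission at 20% / 5% the figures are 45 points (73.8 − 28.8) against 63.1 − 27.7 = 35.

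**4. The hazard ratio that the plan would report.** Simulation, 60,000 patients per arm, same visit grid, Breslow ties (MBC against standard care):

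| Removed, MBC / standard | Response: censored / event-free to week 24 | Remission: censored / event-free to week 24 |
|---|---|---|
| 10% / 10% | 1.84 / 1.80 | 3.45 / 3.37 |
| 15% / 5% | 1.84 / 1.62 | 3.49 / 3.11 |
| 5% / 15% | 1.85 / 2.00 | 3.42 / 3.70 |

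With equal removal the change is 2% (1.80/1.84 = 0.98; 3.37/3.45 = 0.98). With a 10-point imbalance it is roughly 8–13% across the scenarios run, for example 1.62/1.84 = 0.88 and 2.00/1.85 = 1.08.

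**5. What counting removal as failure does when response is unaffected.** With identical underlying rates in both arms, the censored hazard ratio is about 1.0. The event-free rule gives 0.91–0.92 when MBC loses 15% and standard care 5%, and 1.09–1.10 when these are reversed. With 60 per arm and 5% MBC / 20% standard removed, a log-rank test at 0.05 rejects in about 5% of trials under censoring and in about 10–11% under the event-free rule.

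**The case against.** A reader might infer that the plan turns treatment failures into neutral censoring, and that the share-of-randomised figures are the true differences, which Kaplan-Meier misstates. The documents do not support either step.

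- **No rule says removed patients are censored.** The protocol says all are followed for 24 weeks, and the SAP places analysis after follow-up of all recruited participants. Censoring is the likely default of an unspecified plan. This stands.
- **The calculation does not demonstrate a bias.** Removal is independent of response in it, so Kaplan-Meier is correct for its own question. The gap arises because removal is redefined as failure, and because patients who go on to receive treatment elsewhere are assumed not to respond. This stands.
- **The removal rates are assumed, and 20% may be high.** The side-effect criterion is narrow, one change of drug is allowed, and patients with a suicide attempt in the current episode are excluded at entry. This stands; the balanced 10% case is the milder reading.
- **The dropout hypothesis concerns dropout in general, not these removals.** If standard care did lose more patients, censoring would give the smaller MBC benefit (24 against 31 points). This stands: the direction is open.
- **Removals would still be visible**, since discontinuation and side effects are compared between arms. This stands in part. They would not show in the primary curves, and the SAP keeps all-cause discontinuation but not the cause-specific comparison that the protocol names.

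None of this removes the conflict over follow-up, or the loss of HDRS data in patients whose removal is plausibly related to outcome.

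**Conclusion.** The point holds as a conflict within the protocol and a gap in the SAP. Removal from the study ends primary-outcome collection selectively, and nothing states how those patients are analysed. It does not hold as a demonstrated bias in a known direction.

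If removals are few and balanced, the consequence is small: about 24 against 23 points for response at 10% in each arm, and a hazard ratio changed by about 2%. If they differ by 10 points between arms, the two treatments of removal differ by about 8–13% in the hazard ratio. At 5% against 20%, the response difference moves from 24 to 31 or 15 points, depending on the arm. All of this rests on assumed removal rates, constant hazards and removal independent of response. If removal is related to response, Kaplan-Meier itself would be biased, by an amount that the documents give no means to estimate.

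Nor is counting removal as failure the correction. It is a legitimate different estimand that mixes tolerability into time to response, so it belongs in a sensitivity analysis. The change should be made; it is a cheap improvement to both primary analyses, not a defect that invalidates the design.

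**What to change.** 1. **Protocol, Study Intervention and Procedure and Ethical and safety considerations.** Reconcile the two by distinguishing stopping study medication from leaving the study. Leave the stopping criteria as they are. Continue blinded HDRS at the already scheduled weeks for all removal reasons, including pregnancy and severe medical condition, unless consent is withdrawn.
2. **SAP section 3.2.** State that all randomised patients are analysed as assigned for both primary outcomes, using HDRS collected after removal, and that all randomised patients form the denominator for response and remission rates.
3. **SAP section 3.2, where no HDRS exists after removal.** Report censoring at the last assessment alongside a prespecified sensitivity analysis. This keeps patients removed for a suicide attempt or intolerable side effects event-free to week 24, or treats removal as a competing event.

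**Cost.** A few more assessments at scheduled weeks, some SAP wording, and possibly lower response and remission percentages. The SAP already reports in the past tense that no interim analysis was done, so conduct may be well advanced. If follow-up is complete, item 1 can no longer recover data, but items 2 and 3 still apply.
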